### 3. STUDY DESIGN

#### 3.1 Design

COVID-RED is a randomized, single-blinded, two-period, two-sequence crossover trial. 20,000 subjects will be recruited, randomized 1:1 to either Sequence 1 (experimental condition followed by control condition) or Sequence 2 (control condition followed by experimental condition). The study will start with a Learning Phase (maximum of 3 months), followed by Period 1 (3 months), and Period 2 (3 months) (Table 1). All subjects will be instructed to log symptoms in the Daily Symptom Diary within the Ava COVID-RED app, and wear the Ava bracelet each night and synchronise it with the app each following day, throughout the full period (up to 9 months) of their study participation. In the Learning Phase baseline physiological parameters of subjects will be determined and data will be collected for further algorithm development. Subjects will receive real-time recommendations (for example, to get tested) based on data from the Daily Symptom Diary and/or physiological data from the Ava bracelet. Subjects entering the study at the end of the recruitment period may directly start with Period 1 and will not be part of the Learning Phase.

After completion of the Learning Phase subjects will move into Period 1, followed by Period 2, and will be unaware whether the feedback they receive during these periods is based on the Daily Symptom Diary data alone (control condition) or based on the diary and bracelet data (experimental condition). Based on demographics, medical history and/or profession, each subject will be stratified at baseline into a high-risk and normal-risk group within each sequence. This results in approximately 6,500 normal-risk individuals and 3,500 high-risk individuals per sequence. See Table 1 for a tabular representation of this design.

Table 1 Crossover trial design for COVID-RED

|                                                               | Learning Phase
(up to 3 months) | Period 1
(3 months) | Period 2
(3 months) |
|---------------------------------------------------------------|-------------------------------------------|-------------------------------|-------------------------------|
| Sequence 1
(6,500 normal-risk &
3,500 high-risk) | Algorithm training &
baselining        | Experimental
Condition     | Control
Condition          |

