#### *Analysis sets*

Several analysis sets will be defined which will be used for the analyses described in the following sections:

- **Intention-to-treat set:** All subjects randomized to one of the two study sequences. For the analysis, subjects will be considered part of the study sequence that they were originally randomized to. Note that when a subject has their first SARS-CoV-2 infection (as confirmed through a positive PCR/antigen or serology test), they will no longer be part of the analysis going forward because they have met the primary outcome.

- **Efficacy analysis set:** All compliant subjects randomized to one of the two study sequences, where compliance is defined as having entered symptom data in the Ava COVID-RED app on at least 80% of the days of Period 2 **and**, when in the experimental condition, having worn and synchronised the Ava bracelet on at least 80% of the days of Period 2.
- **Partial compliance set:** All subjects randomized to one of the two study sequences that were partially compliant; which is defined as having entered symptom data in the Ava COVID-RED app on at least 80% of the days of Period 2 **or**, when in the experimental condition, having worn and synchronised the Ava bracelet on at least 80% of the days of Period 2.
- **Safety analysis set:** All subjects who were randomized and received an Ava bracelet.

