### 10.2 Primary Analysis of Primary Endpoint(s)

The primary analysis of the primary endpoint will compare the performance of the algorithm applied in each study condition to detect if subjects were ever infected during Period 2. This analysis will be performed on both the Intention-to-treat and Efficacy analysis sets, within each period and stratified per risk group. For the subjects within each study condition, the daily prediction of possible SARS-CoV-2 infection and the results of PCR/antigen and serology tests will be summarized over the whole period per subject to determine (1) if a subject was ever judged to have a high risk for a potential SARS-Cov-2 infection (i.e. received a red-light indicator from the Ava COVID-RED app), and (2) if a subject was ever confirmed to have a SARS-CoV-2 infection by PCR/antigen or serology testing. For this comparison, parameters such as sensitivity, specificity, positive predictive value, and negative predictive value will be calculated.

To confirm whether a subject was ever infected in Period 2 with SARS-CoV-2, the serology status at the end of Period 2 for each subject still alive at that time will be used as the gold standard. Those with a previous positive test result will be excluded from the analysis. For subjects not alive at the end of Period 2, the status of available SARS-CoV-2 virus tests during Period 2 will be used (positive at any time) and for those without any test results, a physician diagnosis during Period 2 will be accepted provided there was a supportive lung CT scan used. All other subjects will be summarized for transparency but excluded from the estimation for sensitivity, specificity, positive predictive value and negative predictive value.

The following quantities are needed for these statistics:

- **Predicted condition positive:** The total number of subjects that obtained a red-light indicator from the Ava COVID-RED app at least once during Period 2.
- **Predicted condition negative:** The total number of subjects that never obtained a red-light indicator from the Ava COVID-RED app during Period 2.
- **Condition positive:** The total number of subjects who tested positive at least once using SARS-CoV-2 virus testing during Period 2 OR who had a positive serology test at the end of Period 2.
- **Condition negative:** The total number of subjects who never tested positive for the SARS-CoV-2 virus during Period 2 AND who had a negative serology test at the end of Period 2.

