### 10.5 Analysis of Secondary Endpoint(s)

Secondary study endpoints mentioned in section 8.1.2 will be analysed and compared within the Intention-to-treat, Efficacy analysis and Partial compliance sets within each period. Where deemed relevant, analyses will also be executed within selected subsets of these analysis sets. Specific subsets will be listed within the Statistical Analysis Plan. Results will be presented in tables where possible. Where percentages are to be calculated, the number of subjects in the condition within the specified analysis (sub)set will be used as the denominator.

Where assumptions are met, Cochran-Mantel-Haenszel tests stratified by the risk strata will be performed in each period for multiple secondary endpoints, including:

- The number and percentage of subjects that obtained a red-light indicator by the applied algorithm at least once.
- The number and percentage of subjects with at least one positive SARS-CoV-2 virus test result during follow-up.

- The number and percentage of subjects that donated a blood sample for a SARS-CoV-2 antibody test at baseline, after the Learning Phase and after both periods.
- The number and percentage of subjects with a positive SARS-CoV-2 antibody test at baseline, after the Learning Phase and after both periods.
- The number and percentage of subjects with at least one positive SARS-CoV-2 virus test result during each period OR a positive SARS-CoV-2 antibody test result within those periods.
- The number and percentage of subjects without a positive SARS-CoV-2 virus test result during each period AND a negative SARS-CoV-2 antibody test result within those periods.
- The number and percentage of subjects that have reported experiencing each of the symptoms listed in the Ava COVID-RED app at least for one day during the study.
- The number and percentage of subjects that have reported experiencing each of the symptoms corresponding by the RIVM guidelines at least for one day during the study.
- The number of subjects who reported a positive SARS-CoV-2 virus test during the study and the percentage of subjects who reported a positive SARS-CoV-2 virus test during the study, with the number of subjects ever receiving a PCR test during the study as the denominator.

Where assumptions are met, t-tests will be performed in each period for multiple secondary endpoints, including:

- The average and median number of times a single subject obtained a red-light indicator by the applied algorithm.

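### The default denominator in section 10.5 keeps subjects whose infection status is unknown, and direct entrants with no Learning Phase sample, so the infected percentages are understated whenever serology is missing

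*Protocol*

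**What the plan says.** Section 10.5 of the protocol applies this rule to secondary endpoints: "Where percentages are to be calculated, the number of subjects in the condition within the specified analysis (sub)set will be used as the denominator". The analyses run in the Intention-to-treat, Efficacy and Partial compliance sets. The first of these is defined as "All subjects randomized to one of the two study sequences". The other two are defined by diary and bracelet use in Period 2. None of the three requires a serology result. After a first confirmed infection, subjects leave later analyses: "they will no longer be part of the analysis going forward because they have met the primary outcome".

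Three kinds of row in 10.5 depend on serology and have no denominator of their own:

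- Antibody-positive: "The number and percentage of subjects with a positive SARS-CoV-2 antibody test at baseline, after the Learning Phase and after both periods".
- Infected (combined): subjects "with at least one positive SARS-CoV-2 virus test result during each period OR a positive SARS-CoV-2 antibody test result within those periods".
- Not infected: subjects "without a positive SARS-CoV-2 virus test result during each period AND a negative SARS-CoV-2 antibody test result within those periods".

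One other row, on self-reported positive virus tests, does have its own denominator: subjects ever PCR tested. Section 10.5 also reports sample donation as a separate row.

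Section 10.2 handles subjects without a usable status differently for its accuracy measures: "All other subjects will be summarized for transparency but excluded from the estimation for sensitivity, specificity, positive predictive value and negative predictive value".

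Section 3.1 lets late recruits skip the Learning Phase: "Subjects entering the study at the end of the recruitment period may directly start with Period 1 and will not be part of the Learning". Section 8.4.8 gives these direct entrants three samples, none of them at the end of the Learning Phase. It also says that the Period 1 sample is analysed only when the Period 2 sample is positive, and that infection status is expected to be known for nearly everyone.

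**The concern.** A percentage reads as an infection rate only if everyone in its denominator could have been found infected. Under the 10.5 default, a subject with no serology and no positive virus test cannot reach the numerator of either infected row but is still in the denominator. The published percentage then mixes the infection rate with the rate of returning usable samples.

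These rows bear on secondary objective 2, the incidence of infection during the study, and 10.5 lists them for Cochran-Mantel-Haenszel tests between conditions. Section 10.5 shows that a row can be given its own denominator, but does so only for the PCR-tested row. An SAP that follows the protocol would carry the default forward.

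The Learning Phase rows have a separate problem that does not depend on compliance. Direct entrants to Period 1 are never asked for that sample, yet they count in its denominator.

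**Working it through.** The protocol states no incidence, no sample-return rate and no power for these rows, so there is no figure to reproduce. The check is algebra with stated assumptions.

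**Inputs**

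- p, true period infection rate. For illustration, the lowest and highest rates from Table 2 in section 4.4: 5,427/180,182 = 3.01% (Week 36) and 23,264/223,274 = 10.42% (Week 40). These are shares of tested people found positive, borrowed because the protocol uses them for its own power figures.
- m, share without a serology result, taken as missing at random. Not in the documents; shown from 1% to 30%.
- d, share of infected subjects without serology who have a positive virus test. Not in the documents; shown at 0, 0.5 and 0.8.
- 10,000 subjects per condition (section 4.4.1); two-sided 0.05 (section 10).

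**Step 1: who is counted where (10.5 default)**

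- Antibody-positive row: p(1-m). Relative understatement m.
- Combined infected row: p(1-m) + pmd = p[1 - m(1-d)]. Relative understatement m(1-d).
- Not-infected row: (1-p)(1-m), because a negative antibody result is required.
- Neither combined nor not-infected row: the remainder.

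**Step 2: combined infected row, true p = 10.42%**

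| m | d = 0 | d = 0.5 | d = 0.8 |
|---|---|---|---|
| 1% | 10.32% | 10.37% | 10.40% |
| 5% | 9.90% | 10.16% | 10.32% |
| 10% | 9.38% | 9.90% | 10.21% |
| 20% | 8.34% | 9.38% | 10.00% |
| 30% | 7.29% | 8.86% | 9.79% |

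With p the antibody-positive rate, the d = 0 column also gives the antibody row. At p = 3.01% and d = 0 the values are 2.98, 2.86, 2.71, 2.41 and 2.11%. At m = 20% the relative understatement is 20% for d = 0, 0.20 × 0.5 = 10% for d = 0.5, and 0.20 × 0.2 = 4% for d = 0.8.

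**Step 3: where the unknown subjects go (p = 10.42%, m = 20%, d = 0.5)**

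Infected 10.42% × 0.9 = 9.38%. Not infected 89.58% × 0.8 = 71.66%. Neither 100 - 9.38 - 71.66 = 18.96%. Both listed percentages are too low, and the unknown group is the gap between their sum and 100%.

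**Step 4: Learning Phase rows**

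If a share e of the analysis set entered Period 1 directly, the after-Learning-Phase antibody row shows p(1-e) even with m = 0. The relative understatement is e. The documents do not give e.

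**Step 5: would the 10.2 definitions serve as denominator?**

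The 10.2 condition-positive group accepts a positive virus test without serology; the condition-negative group requires negative serology. Their sum as denominator gives [p(1-m) + pmd] / [(1-m) + pmd]. At p = 10.42%, m = 20%, d = 0.5: (8.34% + 1.04%) / (80% + 1.04%) = 11.57%. That overstates a true 10.42% by more than the present rule (9.38%) understates it.

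**Step 6: between-condition comparison**

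Equal m in both conditions leaves the ratio at 1.00. If m were 10% in one and 20% in the other at equal true incidence, the ratio is 0.90/0.80 = 1.125 for d = 0 and 0.95/0.90 = 1.056 for d = 0.5. An unstratified two-proportion comparison with 10,000 per condition then rejects with probability 0.27 (p = 3.01%) to 0.74 (p = 10.42%) for d = 0, and 0.10 to 0.24 for d = 0.5.

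**The case against.** The strongest reply is that the plan does not hide these subjects. Unknown subjects are not put in the not-infected row, sample donation is reported separately, and section 10 promises counts of missing data, with imputation where necessary. Section 8.4.8 expects status to be nearly complete. The 10.5 rule also allows subsets that the SAP will list, so a serology-available subset could satisfy it. Much of this stands: a careful reader could see the gap and rescale. It does not correct the percentages or the tests that 10.5 specifies in the three named sets, and imputation is not tied to these rows.

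Three stronger readings are tempting and are not supported.

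- A reader might infer that everyone without serology is counted as uninfected. A positive virus test alone counts as infected in the combined row, and the not-infected row requires a negative antibody result.
- A reader might infer that 10.5 contradicts 10.2. The 10.2 exclusion covers only sensitivity, specificity and the two predictive values, and 10.2 has fallbacks for subjects who have died. Handling differs between analyses; the two rules do not collide.
- A reader might infer a false difference between conditions. Allocation is 1:1, subjects are blinded, and nothing in the documents indicates unequal sample return. Step 6 shows what would follow if it occurred, not that it will.

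**Conclusion.** The point holds in limited form. The default denominator understates the infected percentages whenever serology is missing: by m in the antibody row and by m(1-d) in the combined row, in relative terms. At an assumed m = 20% the combined-row effect ranges from 4% (d = 0.8) to 20% (d = 0). At m = 1% it is at most 1%, and it vanishes if serology is complete. Neither m nor d is in the documents, so the actual size is unknown. The results assume serology is missing at random.

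The Learning Phase denominator is wrong regardless of compliance whenever there are direct entrants, by the share of such entrants.

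The primary accuracy analysis is not affected. Section 8.1.2 lists cumulative incidence without giving a denominator, so carrying the same bias over to that endpoint would be an inference. The change is worth making because it corrects a stated rule at little cost.

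**What to change.** In section 10.5:

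- For the antibody-positive, combined-infection and not-infected rows, use as denominator the subjects with a determinable serology status at that time point, and take the numerator from the same subjects. The infected and not-infected percentages then add to 100.
- Count a sample left unanalysed by design because the later sample was negative as known negative. This follows the testing logic of section 8.4.8, which uses the same assay type within each pair of samples. A subject with no Period 2 sample, whose Period 1 sample is therefore never analysed, is unknown.
- Do not use the 10.2 positive and negative definitions as the denominator. They keep virus-positive subjects without serology, drop the others without serology, and overstate incidence (11.57% for a true 10.42% in step 5).
- Limit Learning Phase rows, including sample donation, to subjects who took part in that phase.
- Report the number with unknown status in its own row, by condition and risk stratum.
- Give the all-subjects percentage, with virus-positive subjects without serology counted as infected, as a sensitivity analysis.

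The cost is a wording change and fewer subjects per percentage: at m = 20%, standard errors grow by a factor of 1/√0.8 = 1.12. Virus-positive subjects without serology move from the main percentage to the sensitivity analysis. The main percentage then rests on serology being missing at random; if sample return depends on infection, it is biased too, which is why the sensitivity analysis and the unknown count are needed.

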During the study, the algorithms in both the control and experimental conditions will provide real-time prediction to subjects whether they likely have an active SARS-CoV-2 infection. Individuals with a suspected SARS-CoV-2 infection based on these algorithms will be encouraged to get tested using the existing testing infrastructure in the Netherlands provided by the Municipal Health services (GGD). At the moment of writing, the GGD offers free SARS-CoV-2 polymerase chain reaction (PCR) and antigen testing services. While in this protocol tests to confirm current SARS-CoV-2 infection are described as PCR and/or antigen tests, results from other validated testing methods used by the GGD will also be documented and processed in the same way, should the GGD choose to expand the type of tests being used to detect SARS-CoV-2 infection in Dutch residents. Subjects who are thought to have an SARS-CoV-2 infection according to the algorithm of the control or experimental condition, but are rejected for testing by the GGD, will be advised to use self-sampling kits provided by the study team which they can send to the central laboratory for testing. A reason for such rejection by the GGD may include not (yet) having overt symptoms of a respiratory tract infection plus not having any evidence (such as a GGD or CoronaMelder app notification) of having been in close contact with someone who tested SARS-CoV-2-positive. In addition, fingerstick capillary blood samples will be collected from COVID-RED subjects at baseline, after the Learning Phase (if applicable) and after the completion of each period. Samples collected after the Learning Phase and the completion of Period 2 will be tested for SARS-CoV-2 antibodies to determine whether the subject had a previous SARS-CoV-2 infection prior to the study or during the test periods (which was not detected through real-time SARS-CoV-2 infection testing). Baseline samples of subjects will only be analysed if the sample collected at the end of the Learning Phase is positive for SARS-CoV-2 antibodies or if the subject entered the study at the end of the recruitment Period. Samples of subjects collected at the end of Period 1 will only be analysed if the sample collected at the end of Period 2 is positive for SARS-CoV-2 antibodies.

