### **3.5 SARS-CoV-2 infection testing**

This study will use the existing testing infrastructure in the Netherlands provided by the Municipal Health services (GGD). At the time of writing, any citizen of the Netherlands has access to free polymerase chain reaction (PCR) or antigen testing for SARS-CoV-2 if they experience any of the specific symptoms defined by the RIVM guidelines (at the time of writing, these include: common cold symptoms [such as a nasal cold, runny nose, sneezing, sore throat], coughing, shortness of breath, elevated temperature or fever, and sudden loss of smell and/or taste [without nasal congestion]). As per 1 December 2020, asymptomatic persons who have been in close contact with someone who tested SARS-CoV-2-positive (as determined by the GGD contact-tracing program or by the CoronaMelder app) will also qualify for testing. SARS-CoV-2 virus testing procedures at the GGD (types of tests and criteria for testing) may change during the study period; up-to-date testing guidelines are always available on the RIVM website; <https://www.rivm.nl/>. During the study, subjects will be instructed to use GGD testing where possible and appropriate because this will automatically enter them into the national contact-tracing program. The results of the GGD test will be communicated to the subject directly through a web portal or by phone, as is done on a national level for every individual who gets tested. Changes in national testing policy and the types of tests used regionally will be monitored and taken into account where appropriate.

All subjects who receive a red light indication to get testing will be instructed to first contact the GGD for testing. If they do not satisfy the criteria for GGD testing, subjects can use nasal swab sampling kits provided by the study team to collect a sample themselves which they will send to the central study laboratory for testing using provided return envelopes. Subjects will be asked to log all SARS-CoV-2 test results into the Ava COVID-RED app regardless of where the testing was done. Additional details surrounding the location, accessibility and

types of tests will be requested through periodic surveys. The study team will report all subjects who tested positive to the GGD (SARS-CoV-2 is a notifiable disease in the Netherlands) so that the GGD can initiate contact-tracing.

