- The average and median number of continuous days that each symptom in the Ava COVID-RED app was reported to be experienced.
- The average and median number of continuous days that each symptom corresponding to the RIVM guidelines was reported to be experienced.
- The average (and variance) number of days between a red-light indicator of the applied algorithm and the SARS-CoV-2 virus test result, stratified for tests done via the GGD and central laboratory, and also stratified for testing methodology.
- The average (and variance) number of days between a red-light indicator of the applied algorithm and the taking of a SARS-CoV-2 virus test, stratified for tests done via the GGD and central laboratory, and also stratified for testing methodology.

- Number of total SARS-CoV-2 virus tests taken by subjects, stratified for tests taken by GGD and/or central laboratory, and also stratified by testing methodology if applicable (PCR vs. antigen tests).
- The number of total positive SARS-CoV-2 virus tests and percentage of positive tests, with the number of total tests within the study taken as a denominator. This will also be stratified for the different testing methodologies if applicable.
- Average and median duration of Ava bracelet and/or Ava COVID-RED app use (number of days between first day of use and last day of use)
- Compliance rate: percentage of days (as compared to duration of use) that Ava bracelet data was synced to Ava COVID-RED app or symptoms were entered. Upon inspection of the data, other modes (like Poisson regression) will also be considered.

For other relevant endpoints (e.g. survival status of subjects at end of follow-up) appropriate statistical methods (e.g. survival analysis) will be used. Further details will be indicated within a separate statistical analysis plan.

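### Section 10.5 divides subjects positive on any virus test (PCR or antigen) by PCR-tested subjects only, so numerator and denominator do not match

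*Protocol*

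**What the plan says.** Section 10.5 of the protocol sets a general rule for percentages: "the number of subjects in the condition within the specified analysis (sub)set will be used as the denominator". One item in the list of endpoints for Cochran-Mantel-Haenszel tests departs from it. Its numerator is given by "the percentage of subjects who reported a positive SARS-CoV-2 virus test during the study", and its denominator is fixed "with the number of subjects ever receiving a PCR test during the study as the denominator".

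The protocol's use of the term virus test is broader than PCR:

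- In the same section, the count of virus tests taken is "also stratified by testing methodology if applicable (PCR vs. antigen tests".
- Section 1.4 sets the usage for the whole document: "While in this protocol tests to confirm current SARS-CoV-2 infection are described as PCR and/or antigen tests". It adds that other validated methods adopted by the GGD will be handled in the same way.
- Section 3.5 says that the GGD, the first route to testing, offers "free polymerase chain reaction (PCR) or antigen testing for SARS-CoV-2".
- Section 3.5 also says: "Subjects will be asked to log all SARS-CoV-2 test results into the Ava COVID-RED app regardless of where the testing was done".

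A parallel endpoint in section 10.5, counted per test rather than per subject, divides positive virus tests "with the number of total tests within the study taken as a denominator".

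**The concern.** A percentage of subjects needs a numerator that is a subset of its denominator. Here a subject can enter the numerator on an antigen result alone but enters the denominator only through a PCR test. An antigen-only positive is counted above the line and not below it. An antigen-only negative drops out of the denominator altogether.

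Two things are at stake. The reported percentage is not positivity among tested subjects, which is how it would be read. And the item is listed for a stratified comparison between conditions, so a different mix of PCR and antigen testing in the two conditions would shift the percentages even if positivity were the same.

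This is an inconsistent endpoint definition. The protocol prints no value for the percentage, so no figure in it is miscalculated.

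**Working it through.** There is no planned value to reproduce, so the check is algebra followed by an illustration.

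**Notation.** P = subjects with at least one PCR test. A = subjects with antigen tests only. N+ = subjects with any positive virus test. a = A/(P + A), the antigen-only share of virus-tested subjects. p = N+/(P + A), positivity among all virus-tested subjects.

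**Inflation factor.**

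- As written: N+/P.
- Matched: N+/(P + A) = p.
- Ratio: (P + A)/P = 1/(1 - a).

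The ratio depends only on a. It needs no assumption about positivity, nor that PCR and antigen subjects have equal positivity.

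**Inputs for the illustration.** The protocol does not give a, so it is varied from 0 upward as an assumption. For p, Table 2 (section 4.4) gives national test counts for 2020: week 36, 5,427/180,182 = 3.0%; week 40, 23,264/223,274 = 10.4%. These are not trial forecasts of this endpoint.

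| a (assumed) | 1/(1 - a) | As written, p = 3.0% | As written, p = 10.4% |
|---|---|---|---|
| 0 | 1.00 | 3.0% | 10.4% |
| 0.10 | 1.11 | 3.3% | 11.6% |
| 0.25 | 1.33 | 4.0% | 13.9% |
| 0.50 | 2.00 | 6.0% | 20.8% |

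**When the figure would pass 100%.** This requires N+ > P, that is a > 1 - p. At p = 3.0% the antigen-only share must exceed 97.0%. At p = 10.4% it must exceed 89.6%. At an assumed p of 30% it must exceed 70%.

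**The 2x2 table.** Take 10,000 virus-tested subjects, a = 0.50, and p = 10.42% in both the PCR and the antigen-only group (all for illustration).

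- P = 5,000 and N+ = 1,042.
- The negative cell implied by the wording is P - N+ = 5,000 - 1,042 = 3,958.
- PCR-tested subjects with no positive result actually number 5,000 - 521 = 4,479.

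The implied cell is not a count of any group of subjects, so the Cochran-Mantel-Haenszel test has no proper table to work on.

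**Different shares by condition.** With p = 10.42% in both conditions, but a = 0.30 in one and a = 0.50 in the other (assumed):

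- 10.42%/0.70 = 14.9%
- 10.42%/0.50 = 20.8%

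The gap of about 6 percentage points comes from test mix alone.

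**Why the shares could differ.** Sections 3.3 and 3.4 let control red lights arise only from reported symptoms, and under section 3.5 those symptoms qualify for GGD testing of either type. Experimental red lights can also arise from bracelet data. Section 1.4 names the absence of symptoms and of known contact as a reason for GGD refusal, and section 8.4.12 sends refused subjects to a study PCR kit. A lower a in the experimental condition is therefore plausible, but the protocol gives nothing from which to size it.

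**The case against.** **The phrase may be loose shorthand.** Given the usage set in section 1.4, an analyst might count every virus-tested subject without noticing the wording. That makes misreporting less than certain. It does not rescue the sentence, because the denominator is stated outright and overrides the section's general rule. For the same reason it is not a detail left to the separate statistical analysis plan.

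**Sound neighbouring quantities are already planned.** The same list has the percentage of subjects with at least one positive virus test, which falls under the general denominator rule. Positivity per test is planned over all tests and also by methodology. Cumulative incidence is planned in section 8.1.2. This stands and limits the damage. None of these, however, is positivity per tested subject, which this item is meant to give.

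**A reader might infer that the percentage will exceed 100%.** The documents do not support that. At Table 2 positivity it would take an antigen-only share of about 90% or more, nothing in the protocol suggests such a share, and the study's own kits are PCR.

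**A reader might also infer that this wording is what biases the comparison between conditions, and that correcting it removes the bias.** That is too strong. Red lights prompt testing and the algorithms differ by condition, so any denominator of tested subjects is formed after randomisation. The correction removes only the part due to the PCR-only wording. The test is also planned only if its assumptions hold.

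**The size has no anchor.** This is correct: no antigen-only share is given, and at a = 0 there is no error. The sizes are therefore conditional.

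**Conclusion.** The definition is wrong as written. Its numerator covers PCR and antigen tests, its denominator covers PCR only, and the 2x2 table it implies is ill-defined. Relative to positivity among all virus-tested subjects, the percentage is inflated by 1/(1 - a) if any subject had antigen tests only: by 11%, 33% and 100% at assumed shares of 0.10, 0.25 and 0.50, and not at all at zero. If the share differs between conditions, a spurious difference of unknown size is added to the selection that any tested-only denominator has.

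The mismatch itself rests on the text alone and is certain. The sizes rest on assumed shares, and the direction of any difference between conditions is plausible but not established. One secondary percentage is affected. The primary analysis and the sample size do not use it. This is a minor correction.

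**What to change.** Replace the PCR-only denominator with the number of subjects who had at least one SARS-CoV-2 virus test, PCR or antigen, in line with the per-test endpoint in the same section. Also report PCR and antigen separately, each with a numerator and denominator of the same test type. If PCR alone was intended, restrict the numerator to subjects with a positive PCR test instead. Either way, describe the comparison between conditions as one among tested subjects, a group formed after randomisation.

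The cost is one phrase in section 10.5 and the matching table specification. No new data are needed: the two-weekly survey in section 8.4.14 already records whether a test was taken, its type and its result.
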